## Abstract

**Background:**

People with dementia living in care homes often have complex mental health problems, disabilities and social needs. Providing more comprehensive training for staff working in care home environments is a high national priority. It is important that this training is evidence based and delivers improvement for people with dementia residing in these environments. Well-being and Health for People with Dementia (WHELD) combines the most effective elements of existing approaches to develop a comprehensive but practical staff training intervention. This optimised intervention is based on a factorial study and qualitative evaluation, to combine: training on person-centred care, promoting person-centred activities and interactions, and providing care home staff and general practitioners with updated knowledge regarding the optimal use of psychotropic medications for persons with dementia in care homes.

**Design:**

The trial will be a randomised controlled two-arm cluster single blind trial that will take place for nine months across 80 care homes in the United Kingdom.

**Discussion:**

The overarching goal of this trial is to determine whether this optimised WHELD intervention is more effective in improving the quality of life and mental health than the usual care provided to people with dementia living in nursing homes. This study will be the largest and best powered randomised controlled trial (RCT) evaluating the benefits of an augmented person-centred care training intervention in care homes worldwide.

**Trial registration:**

Current controlled trials ISRCTN62237498

Date registered: 5 September 2013

## Background

There are more than 750,000 people with dementia in the United Kingdom, at least 250,000 of whom live in care homes [1]. These are the individuals with the most complex needs, often with cognitive and functional impairments in combination with significant behavioural and psychological symptoms [2,3]. The main staff members providing the frontline care often have minimal formal training, yet are being asked to undertake an extremely challenging role which requires a high degree of skill. One of the consequences of this at a national level has been the widespread use of antipsychotic medication for people with dementia, with widespread adverse consequences including a significant increase in mortality [2,3].

A high priority task is to provide more comprehensive training for staff working in care home environments, but it is important that this training be evidence based and deliver improvement for people with dementia residing in these environments [4]. Several studies have been undertaken evaluating person-centred care (PCC) training as an intervention in cluster randomised controlled trials (RCTs) or intervention studies with a quasi-experimental design. A meta-analysis across these studies has indicated that PCC training does deliver some significant benefits, including a reduction in antipsychotic use and an improvement in symptoms of agitation [4,5]. However, benefits are inconsistent across individual studies and, perhaps most importantly, there is no clear evidence of an improvement in quality of life. Whilst PCC training is of some value, there is a clear need to optimise these interventions.

To take this work forward, the National Institute of Health Research (NIHR) funding the Well-being and Health for People with Dementia (WHELD) programme undertook a factorial study to determine whether social intervention, exercise and formal antipsychotic review added significant benefit to PCC training. Based on the results, an optimised intervention has been developed combining PCC training, social intervention and a modified approach to antipsychotic review. The current study will examine this optimised intervention in a parallel group cluster RCT comparing the intervention to usual care over nine months.

### Rationale for current study

There is strong evidence that a number of interventions confer some benefit, but no single intervention has achieved both an improvement of mental health and a reduction of antipsychotic use in people with dementia; and none of the interventions conferred a direct benefit to the quality of life (QoL) of people with dementia in care homes.

The overarching goal of this programme is to determine whether this optimised WHELD intervention, combining PCC, promoting person-centred activities and interactions and providing care home staff and general practitioners with updated knowledge regarding the optimal use of psychotropic medications for persons with dementia in care homes, is more effective in improving the QoL and mental health than usual care for people with dementia living in nursing homes. This optimised WHELD intervention is based on the findings of the factorial study [6] and qualitative evaluation designed to facilitate the design of the current study; a multicentre, two-arm cluster RCT, which is designed to establish the value of the WHELD intervention.

### Study objectives

The primary objective is to determine whether the optimised WHELD intervention will significantly improve QoL for people with dementia in comparison to the usual care provided in care homes.

Evaluations will be undertaken to understand the breadth of additional benefits conferred by the interventions compared with treatment as usual.

### Secondary objectives

Key secondary objectives will be to determine the specific impact of the optimised WHELD intervention on a range of outcomes including mental health and unmet needs, use of psychotropic drugs, pain, the quality of the interaction of care staff with people with dementia, and a person-centred environment in care home settings and to overall provide a cost-effective, simple and practical intervention.

### Hypotheses

We hypothesise that the intervention will significantly improve several key outcomes. Specifically, we hypothesise that, compared to treatment as usual, the optimised WHELD intervention will:

• Improve the QoL for people with dementia living in care homes

The secondary hypotheses are that the optimised WHELD intervention will:

• Reduce the rate of global deterioration

• Reduce agitation and other behavioural and neuropsychiatric symptoms

• Improve mood and depression

• Reduce the use of antipsychotic and other psychotropic drugs

• Reduce pain

• Reduce unmet needs

• Reduce mortality

• Provide a cost-effective intervention

• Improve the quality of interactions between staff and residents

• Provide a person-centred environment in care home settings

## Methods/design

### Overall design

The study design is a cluster randomised controlled, two-arm trial to be run in up to 80 care homes. It is estimated that each cluster will include a minimum of 12 participants. Each cluster in the optimised WHELD intervention arm will receive the intervention for nine months. Evaluations will be undertaken to understand the breadth of benefits conferred by the intervention to be assessed when used in comparison with the progress of the participants residing in the care homes allocated to the treatment as usual (TAU) trial arm.

### The WHELD intervention

The optimised WHELD intervention consists of a combination of elements taken from the interventions trialled in our previous factorial study [6] to form a single formulated, manualised intervention. The optimised WHELD intervention training will focus on PCC, promoting tailored person-centred activities and interactions, and will provide care home staff and general practitioners with updated knowledge regarding the optimal use and monitoring of psychotropic medications for people with dementia in care homes.

The WHELD package will consist of a PCC intervention, which primarily uses the tools developed in evidence-based approaches for improving care in care homes, which was shown to be effective in previous RCTs [7-9]. Additional supplementary materials have been drawn from the best available training manuals from a robust review of available materials [10-12] conducted as part of the WHELD study. The feasibility of incrementally combining these materials was evaluated in our previous factorial study [6], and the findings have been used to create the current optimised intervention.

The PCC intervention has five foci:

• Embedding an understanding of dementia and PCC

• Developing the staff’s understanding about the relationship between an individual’s experience and that individual’s behaviour and well-being

• Having care homes embed processes for self-assessing how their practices deliver PCC

• Enabling staff to recognise the impact of staff - resident interactions on the care experience

• Having staff and residents implement PCC planning and individualised care practice based on these principles

This intervention will use evidence-based approaches and specific communication skills training to enhance staff-resident interactions. The intervention will also incorporate evidence-based approaches to encourage person-centred activities and interaction.

The intervention will be delivered by trained research therapists, who will receive an intensive ten-day training package, each of whom will coordinate the delivery of the intervention in the care homes, supported as appropriate by senior staff at each centre. Part of the intervention will involve the training of two lead care staff members (WHELD Champions) in each care home over a period of four months (one training day per month) with additional coaching and supervision over the nine-month period, to support their implementation of the intervention, The intervention manual and materials will be made available following publication of trial results and will also be submitted for publication in accordance with the trial internal and external dissemination plan.

### Control arm

The control group will receive TAU. Care homes in the control group will need to demonstrate a minimum acceptable standard of care, and this information will be collected as part of the quality screening at the selection stage.

An inventory of the standard of care of control arm homes will be undertaken, in order to be able to describe the features of the homes and to document the training they access during the course of the intervention delivery period.

Monthly contact with control group care homes will be maintained during the programme, to ensure that Serious Adverse Event (SAE) reporting occurs.

### Design and Consolidated Standards of Reporting Trials (CONSORT) diagram

This will be a pragmatic cluster RCT testing the experimental intervention with a sample of residents with dementia in care homes. The sample will be cluster-randomised by care home, with all recruited residents in a given care home being allocated to either the experimental or control arm. Figure 1 (the design and CONSORT diagram) shows the stages of the trial. Figure 2 shows the programme milestones.

**Figure 1 F1:**
[figure not shown]
Design and CONSORT diagram.

**Figure 2 F2:**
[figure not shown]
Flow chart of WHELD programme milestones.

### Number of participants and power of the study

Up to 80 suitable care homes, or units within larger homes, will be identified, recruited and randomised, and the minimum target participant recruitment is 12 individuals with dementia per care home. Therefore, the target minimum sample size is 960, with a suggested upper recruitment limit of approximately 1,280 (that is, 16 individuals with dementia per care home). There will be no more than two units in any care home.

Baseline and follow-up data will be collected on all consented residents who meet the inclusion criteria at each participating care home. Taking into account the likely loss to follow up, it is estimated that, on average, 8 of the 12 will be followed up at nine months, giving a total sample size of 640. This trial is cluster randomised to take account of the fact that the participants live together in care homes. Re-analysis of data from previous studies suggests that intra-home correlation coefficients rarely exceed 0.05. As the ‘variance inflation factor’ (VIF) of this cluster randomised trial [1 + (8 - 1) × 0.05] = 1.35, the likely useable sample size of 640 participants will give 90% power using a significance level of 5% to detect a standardised effect size of 0.3 SDs, which is usually taken as the lowest threshold of a clinically meaningful benefit [13].

The observed SD for our population on DEMQOL taken from our pilot study is approximately 12. The standard error of measurement (SEM), derived by multiplying the SD of the sample by the square root of one minus its reliability coefficient, has been described as a useful statistic for assessing individual change on health-related QoL instruments [14]. Smith *et al.*[15] reported DEMQOL’s reliability coefficient as 0.82. Therefore, the SEM for this data is 12*sqrt (1-.82) = 5.1. This provides further support that we are measuring clinically meaningful change in DEMQOL [16]. Expressing this change as an effect size gives 5.1/12 = 0.425.

### Randomisation

Care homes will be allocated to either receive the optimised WHELD intervention or TAU using secure web access to the remote randomisation centre at North Wales Organisation for Randomised Trials in Health Clinical Trial Unit (NWORTH CTU), at Bangor University. This system will be set up, maintained and monitored independently of the trial statistician or other trial staff. The randomisation will be performed by dynamic allocation [17] to protect against subversion while ensuring that the trial maintains good balance to the allocation ratio of 1:1 both within each stratification variable and across the trial. Care homes will be stratified by region and size. The system has been coded and validated in the R statistical package.

### Outcome and study eligibility measures

All outcomes will be assessed prior to randomisation and after nine months of the intervention. Outcome measures will consist of questionnaires and direct observations, using standardised, evidence-based scales and other information obtained from an informant (the key worker or another member of the staff who knows the participant well). Participant and care home demographics will be collected and measures taken as described in the following paragraphs.

The DEMQOL [15] assesses the health-related quality of life (HRQoL) for people with dementia. The measure consists of two questionnaires. DEMQOL, conducted with a person with dementia, is a 28-item interviewer-administered questionnaire with a score range of 28 to 112. DEMQOL-Proxy is a 31-item interviewer-administered questionnaire answered by a caregiver with a score range of 31 to 124. The DEMQOL-Proxy is the primary outcome measure for this study. The measure is also validated as a method for calculating quality-adjusted life-year (QALY) for health economic analysis.

The Quality of Life in Late-Stage Dementia (QUALID) scale [18] is a reliable and valid scale, administered to caregivers, for rating quality of life in people with late-stage dementia. The scale measures 11 observable behaviours indicating activity and emotional states. Ratings are made for observations made over the preceding seven days. Items are rated on a five-point Likert scale with QUALID scores ranging from 12 to 45 points; lower scores reflect a higher quality of life (QoL).

The Clinical Dementia Rating (CDR) [19] is a validated scale used to quantify the severity of symptoms of dementia. Using a structured interview, six domains are assessed in terms of a person’s cognitive and functional performance. These include memory, orientation, judgment and problem solving, community affairs, home and hobbies, and personal care. CDR ratings are 0 for healthy people, 0.5 for questionable dementia and 1, 2 and 3 for mild, moderate and severe dementia. Scores in each of these domains are combined to obtain a composite score ranging from 0 (none) through 3 (severe).

The Functional Assessment Staging Tool (FAST) is a validated functional assessment scale of elderly people with dementia [20]. The FAST is an ordinal scale ranging from 1 (indicating normal function) to 7 (indicating severe dementia). Levels 6 and 7 are divided into specific subscales yielding 16 possible ratings. Each level is indicated by a functional description with adequate detail for clinical scoring. The FAST score is derived from a caregiver interview.

The Global Deterioration Scale (GDS) [21] is a staging scale indicating deterioration in dementia. The scale details clinical descriptions of seven major distinguishable stages, ranging from normal cognition to severe dementia. Stages 1 through 3 are the pre-dementia stages, While stages 4 through 7 reflect the stages of dementia. People with clinical levels beginning with stage 5 are no longer able to survive without assistance.

Agitation will be assessed using the Cohen-Mansfield Agitation Inventory (CMAI) [22], which is a caregiver’s rating questionnaire to specify agitated behaviour. The CMAI consists of 29 items related to agitated behaviour, each of which is rated on a seven-point scale of frequency, from 1 = never to 7 = several times an hour. The rating is based on a face-to-face interview with a caregiver.

Other behavioural and neuropsychiatric symptoms will be recorded using the Neuropsychiatric Inventory Nursing Home version (NPI-NH). The NPI is a validated structured interview assessment with the informant (care staff), that assesses behavioural disturbances in patients with dementia [23]. This 12-item version consists of ten behavioural and two neurovegetative areas. It provides both a total score as well as scores for a number of subscales (delusions, hallucinations, agitation/aggression, depression/dysphoria, anxiety, disinhibition, elation/euphoria, apathy/indifference, irritability, aberrant motor activity, sleep, and appetite/eating disorders). The frequency, severity and caregiver distress levels for each domain are measured. The total possible maximum score is 144. A higher score reflects increased frequency and severity of the disturbances. This specific version is developed for use in nursing homes, with adapted questions in the standardised interview, and the caregiver distress assessment is adapted to occupational disruptiveness.

Depression will be assessed using the Cornell Scale for Depression in Dementia (CSDD). The CSDD [24] is an assessment of signs and symptoms of major depression in patients with dementia. The CSDD uses a comprehensive interviewing approach that derives information via semi-structured interviews with the participant and the care staff. Many of the items to be completed during the patient interview can be filled in after direct observation of the patient. The final ratings of the CSDD items represent the rater's clinical impression rather than the responses of the informant or the patient. Each item is rated for severity on a scale of 0 to 2 (0 = absent, 1 = mild or intermittent, 2 = severe), and the item scores are then added. Scores above 10 indicate a probable major depression. Scores above 18 indicate a definite major depression. Scores below 6 as a rule are associated with absence of significant depressive symptoms.

Information on antipsychotic use (number of people taking antipsychotics and dose) will be taken from participants’ drug charts, as will the use of other psychotropic (sedative) drugs and other medication.

The Abbey Pain Scale [25] is an observational brief indicator of pain for people with end-stage dementia. The scale is rated on six non-verbal indicators of pain, where 0 is none and 3 is severe.

The Health Questionnaire (Proxy version EQ-5D-5 L), which is based on the EQ-5D-3 L [26] is used to enable an additional health economic evaluation. The questionnaire is short and brief, but importantly will provide greater comparability with other studies.

The Camberwell Assessment of Need for the Elderly (CANE Version IV) [27] is a comprehensive assessment assessing 24 areas of social, medical, psychological and environmental needs. The overall rating on the CANE will be based on all the information gathered throughout the structured interview with the care staff and on the information collected through looking at the case-note reviews and observations within the care home. We will complete this instrument only after the nine months intervention time point.

We will use the Client Service Receipt Inventory (CSRI) [28] to estimate the cost of service packages for each participant in the study. Information is collected on the current living arrangements, and use of hospital, community-based and day services over a defined retrospective of three months in this study. The data collected through the CSRI will be used to calculate service costs and total costs of care.

The Quality of Interaction Schedule (QUIS) [29] is an observational tool which measures the quality of interactions between staff and resident and person-centred environment in care home settings.

The Enhancing the Healing Environment (EHE) Environmental Assessment Tool [30] is a comprehensive observational assessment of the care environment. Assessors can carry out the assessment primarily by walking through the home and directly observing the building and the way it is used in practice. The EHE Environmental Assessment Tool has been produced by the Department of Health and King’s Fund as part of a national survey; therefore, using this tool in our study will provide benchmarking against national data.

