### Participant selection: inclusion, exclusion and withdrawal criteria

All residents who would be potentially eligible for evaluation will be identified by the care home staff.

Inclusion for evaluation:

• All individuals residing in participating care homes who meet diagnostic criteria for dementia and/or score ‘1’ or greater on the CDR [19].

Exclusion from evaluation:

• Any resident from whom consent or the advice of a consultee cannot be obtained.

Withdrawal criteria:

• Individual participants will be able to withdraw from the study evaluation at any time.

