### Quantitative analysis

Outcome measures for the study will be assessed at baseline and at nine months. All the outcome measures collected will be described and reported using appropriate descriptive statistics and tabular and graphical techniques. Means with 95% confidence intervals will be quoted and a 5% significance level will be reported.

The Consolidated Standards of Reporting Trials (CONSORT) diagram information will be presented in order to identify any differential dropout between the arms of the trial.

The analysis of the quantitative outcomes will involve a multilevel analysis of covariance (ANCOVA). Logistic regression will be used to assess whether the missing status can be predicted from any of the factors and covariates measured at baseline. The variables which are identified to affect the missing status will be included in the analysis model [31]. The primary outcome measure (DEMQOL proxy) [22] and the secondary outcome measures will be analysed using the multilevel modelling approach to ANCOVA. The value at nine months will be the response. The baseline value will be the covariate. The key factor will be group (treatment or control). The multilevel nature of the design will be represented by two levels: care home and individual residents in the care home.

Other covariates, whether at the care home level (for example, number of residents) or the resident level (age, gender) will be investigated to see whether they have an effect on the response measure and included as necessary.

A full statistical analysis plan will be developed through the course of the study.

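### If the CDR is analysed as a nine-month outcome, its 0-3 composite has about three usable levels and a ceiling at 3 in this population; the six domain ratings behind it give a finer score

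*Protocol article*

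**What the plan says.** The section on outcome and study eligibility measures opens by fixing the timing: "All outcomes will be assessed prior to randomisation and after nine months of the intervention". It then describes the scales one after another without saying which are outcomes and which serve eligibility only. For the CDR it says "Using a structured interview, six domains are assessed in terms of a person’s cognitive and functional performance", that "CDR ratings are 0 for healthy people, 0.5 for questionable dementia and 1, 2 and 3 for mild, moderate and severe dementia", and finally "Scores in each of these domains are combined to obtain a composite score ranging from 0 (none) through 3 (severe". It mentions no sum of the domain scores.

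The participant selection section admits residents "who meet diagnostic criteria for dementia and/or score ‘1’ or greater on the CDR". This is the only use of the CDR that the article names.

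The secondary hypotheses include "Reduce the rate of global deterioration", with no instrument attached. Two other staging scales are collected: the GDS, with seven stages of which 4 to 7 are dementia, and the FAST, for which "Levels 6 and 7 are divided into specific subscales yielding 16 possible ratings".

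Under Quantitative analysis, "the secondary outcome measures will be analysed using the multilevel modelling approach to ANCOVA", with the nine-month value as response and the baseline value as covariate.

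**The concern.** Read together, these sections put a five-level stage score into a linear model for change over nine months, in a population selected toward the top of that scale. A resident at 3 has nowhere to go. A resident at 1 or 2 must cross a whole stage in nine months before any change registers. Benefit or harm in residents held at the ceiling, or moving within a stage, does not reach the analysis. The estimated difference on the CDR is then smaller than the difference in underlying severity, and noisier relative to its size. The composite is built from six ratings that hold more information, so the loss can largely be avoided at no cost in data collection.

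**Working it through.** **The plan's own figure.** The article gives no power for the CDR. Its only power statement concerns the primary outcome: 640 followed up, variance inflation factor 1.35, effect 0.3 SD, 5% significance (taken as two-sided), 90% power. Effective N = 640/1.35 = 474, or 237 per arm. Power = Φ(0.3·√(237/2) − 1.96) = Φ(3.27 − 1.96) = 90.4%. The stated figure reproduces. It is used below only as a yardstick.

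**Counting levels.** The ratings are 0, 0.5, 1, 2 and 3.
- Composite: five levels, three of them at or above 1.
- Sum of six domains, assuming each domain uses the same five ratings: 0 to 18 in half-point steps gives 37 values. Of these, 16.5 and 17.5 cannot occur, because one domain at 0.5 limits the total to 5 × 3 + 0.5 = 15.5. That leaves 35 values.
- If every domain is at least 1, the sum runs from 6 to 18, giving 13 values against the composite's three.

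**Loss from cutting a severity score to 1/2/3, without baseline adjustment.** Let severity be normal and let the stage be severity cut at two points. The share of information kept is the squared correlation between stage and severity: [φ(c1) + φ(c2)]² / Var(stage). Worked case, with 20%, 40% and 40% at stages 1, 2 and 3: the cuts are −0.842 and 0.253, so φ = 0.280 and 0.386, which sum to 0.666. The stage mean is 2.2 and its variance 0.56. Efficiency = 0.666²/0.56 = 0.79. Power for a 0.3 SD effect on underlying severity follows by replacing 0.3 with 0.3·√efficiency.

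| Assumed share at 1 / 2 / 3 | Efficiency against the uncut score | Power (uncut 90.4%) |
|---|---|---|
| 20 / 40 / 40% | 0.79 | 83% |
| 20 / 30 / 50% | 0.76 | 81% |
| 15 / 25 / 60% | 0.70 | 78% |
| 10 / 20 / 70% | 0.62 | 73% |
| 5 / 15 / 80% | 0.51 | 65% |

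**Composite against the six-domain sum, with baseline as covariate.** This is closer to the planned analysis. Simulations used six correlated domains, a median-type composite, entry at composite 1 or above, and ANCOVA of the nine-month score on its own baseline. Efficiency is the squared ratio of the treatment z-statistics.
- With 34-73% at CDR 3 on entry, it was 57% falling to 46%.
- A second set of assumptions, with 33-79% at CDR 3, gave 62% falling to 54%.
- A third, with 18-69% at CDR 3, gave about 43-55%.

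Rounded, the range is 45-60%. The loss is larger than in the table mainly because a coarse baseline also explains less of the nine-month variation, so the composite loses on both sides of the model. Ignoring clustering, 45-60% is roughly as if 0.45 × 640 = 288 to 0.60 × 640 = 384 residents had been analysed on the domain sum.

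**What remains of the ceiling.** In the first set, 34-73% were at the maximum on the composite and 11-41% on the sum. In the second, 33-79% fell to 12-51%.

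**The case against.** The strongest reply is that the article never names the CDR as an outcome. The list it appears in mixes outcome and eligibility measures, its one assigned use is eligibility, and the scoring sentence may simply describe the instrument. The GDS is by name the closer match to the deterioration hypothesis, and a full analysis plan, not shown here, is promised. This stands in part: the point is conditional on the CDR being analysed at nine months. It does not remove the point, because the timing statement covers all outcomes without exempting the CDR, and the only CDR score described is the composite.

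Four stronger readings are tempting, and the documents do not support them.
- A reader might infer that the trial cannot detect deterioration. FAST has 16 ratings, with its subdivisions in levels 6 and 7 where extra resolution at the severe end is needed, and the GDS is collected too.
- A reader might infer that the CDR sum should decide the deterioration hypothesis. Nothing shows that it outperforms FAST, and the choice of deciding scale is ordinary analysis-plan content.
- A reader might take entry to require CDR 1 or more. The criterion is and/or, so a diagnosed resident at 0.5 is eligible. Hence about three levels, not exactly three.
- A reader might take the background's account of complex needs as evidence that CDR 3 is common. It gives no CDR distribution.

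**Conclusion.** The point holds conditionally. Followed as written, any analysis of the CDR at nine months uses a score with about three usable levels that cannot worsen from 3, and this loses precision and attenuates the treatment difference. Under the assumed mixes the composite keeps roughly 45-60% of the efficiency of the domain sum. That range depends on the assumed share at CDR 3, the correlation between domains, the median-type composite and the size of change, none of which the article gives; other plausible assumptions could move it somewhat outside the band. The direction follows from the level count alone. The consequence is confined to a secondary analysis: DEMQOL-Proxy, the sample size and the error rate of the primary test are untouched.

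**What to change.** State the role of the CDR. Keep the 0-3 composite for eligibility and for tabulating stage. If the CDR is analysed as a nine-month outcome, make the response the sum of the six domain ratings (0-18, provided each domain is rated 0-3), with the baseline sum as covariate in the planned multilevel model. Report by arm the share of residents at the maximum at baseline, on both the composite and the sum, so that a null result can be read against the size of the ceiling. If the CDR is for eligibility only, one sentence saying so closes the matter.

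The cost is wording in the analysis plan, plus retaining the domain ratings in the database rather than only the derived stage. The downsides are that a sum is less familiar to clinicians than a stage, which the tabulation covers, and that residents at 3 in all six domains remain at the maximum.
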